## APPENDIX 6 – REVISED RESPONSE CRITERIA FOR MYELOFIBROSIS

Ref: Tefferi *et al.* (2013). Revised response criteria for myelofibrosis: International Working Group-Myeloproliferative Neoplasms Research and Treatment (IWG-MRT) and European LeukemiaNet (ELN) consensus report. Blood **122** (8) 1395-1398 [2].

These criteria will be used to assess the endpoints of maintenance of response (no evidence of disease progression) in patients with MF and response assessment at 24 weeks.

| Response categories                                                               | Required criteria (for all response categories, benefit must last for ≥12 wk to qualify as a response)                                                                                                                                                                                                                                                                                                                                                                                                                                                                                                                                                                           |
|-----------------------------------------------------------------------------------|----------------------------------------------------------------------------------------------------------------------------------------------------------------------------------------------------------------------------------------------------------------------------------------------------------------------------------------------------------------------------------------------------------------------------------------------------------------------------------------------------------------------------------------------------------------------------------------------------------------------------------------------------------------------------------|
| CR                                                                                | Bone marrow:* Age-adjusted normocellularity; <5% blasts; ≤grade 1 MF† and
Peripheral blood: Hemoglobin ≥100 g/L and <UNL; neutrophil count ≥ 1 x 10  /L and <UNL;
Platelet count ≥100 x 10  /L and <UNL; <2% immature myeloid cells‡ and
Clinical: Resolution of disease symptoms; spleen and liver not palpable; no evidence of EMH                                                                                                                                                                                                                                                                                                            |
| PR                                                                                | Peripheral blood: Hemoglobin ≥100 g/L and <UNL; neutrophil count ≥1 x 10  /L and <UNL; platelet count ≥100 x 10  /L and <UNL; <2% immature myeloid cells‡ and
Clinical: Resolution of disease symptoms; spleen and liver not palpable; no evidence of EMH or
Bone marrow:* Age-adjusted normocellularity; ,
<5% blasts; ≤grade 1 MF†, and peripheral blood: Hemoglobin ≥85 but <100 g/L and <UNL; neutrophil count ≥1 x 10  /L and <UNL; platelet count ≥50, but <100 x 10  /L and <UNL; <2% immature myeloid cells‡ and
Clinical: Resolution of disease symptoms; spleen and liver not palpable; no evidence of EMH |
| Clinical Improvement                                                              | The achievement of anemia, spleen or symptoms response without progressive disease or increase in severity of anemia, thrombocytopenia, or neutropenia§                                                                                                                                                                                                                                                                                                                                                                                                                                                                                                                          |
| Anaemia Response                                                                  | Transfusion-independent patients: a ≥20 g/L increase in hemoglobin level  
Transfusion-dependent patients: becoming transfusion-independent¶                                                                                                                                                                                                                                                                                                                                                                                                                                                                                                                                  |
| Spleen response#                                                                  | A baseline splenomegaly that is palpable at 5-10 cm, below the LCM, becomes not palpable** or
A baseline splenomegaly that is palpable at >10 cm, below the LCM, decreases by ≥50%***
A baseline splenomegaly that is palpable at <5 cm, below the LCM, is not eligible for spleen response
A spleen response requires confirmation by MRI or computed tomography showing ≥35% spleen volume                                                                                                                                                                                                                                                                            |
| Symptoms response                                                                 | A ≥50% reduction in the MPN-SAF TSS††                                                                                                                                                                                                                                                                                                                                                                                                                                                                                                                                                                                                                                            |
| Progressive disease                                                               | Appearance of a new splenomegaly that is palpable at least 5 cm below the LCM or
A ≥100% increase in palpable distance, below LCM, for baseline splenomegaly of 5-10 cm or
A 50% increase in palpable distance, below LCM, for baseline splenomegaly of >10 cm or
Leukemic transformation confirmed by a bone marrow blast count of ≥20% or
A peripheral blood blast content of ≥20% associated with an absolute blast count of ≥1 x 10(9)/L that lasts for at least 2 weeks                                                                                                                                                                                         |
| Stable disease                                                                    | Belonging to none of the above listed response categories                                                                                                                                                                                                                                                                                                                                                                                                                                                                                                                                                                                                                        |
| Relapse                                                                           | No longer meeting criteria for at least CI after achieving CR, PR, or CI, or
Loss of anemia response persisting for at least 1 month or
Loss of spleen response persisting for at least 1 month                                                                                                                                                                                                                                                                                                                                                                                                                                                                            |
| Recommendations for assessing treatment-induced cytogenetic and molecular changes |                                                                                                                                                                                                                                                                                                                                                                                                                                                                                                                                                                                                                                                                                  |
| Cytogenetic remission                                                             | At least 10 metaphases must be analyzed for cytogenetic response evaluation and requires confirmation by repeat testing within 6 months window
CR: eradication of a pre-existing abnormality
PR: ≥50% reduction in abnormal metaphases
(partial response applies only to patients with at least ten abnormal metaphases at baseline)                                                                                                                                                                                                                                                                                                                                    |
| Molecular remission                                                               | Molecular response evaluation must be analyzed in peripheral blood granulocytes and requires confirmation by repeat testing within 6 months window
CR: Eradication of a pre-existing abnormality
PR: ≥50% decrease in allele burden
(partial response applies only to patients with at least 20% mutant allele burden at baseline)                                                                                                                                                                                                                                                                                                                                      |
| Cytogenetic/molecular relapse                                                     | Re-emergence of a pre-existing cytogenetic or molecular abnormality that is confirmed by repeat testing                                                                                                                                                                                                                                                                                                                                                                                                                                                                                                                                                                          |

EMH, extramedullary hematopoiesis (no evidence of EMH implies the absence of pathology- or imaging study-proven nonhepatosplenic EMH); LCM, left costal margin; UNL, upper normal limit.

\*Baseline and posttreatment bone marrow slides are to be interpreted at one sitting by a central review process. Cytogenetic and molecular responses are not required for CR assignment.

†Grading of MF is according to the European classification Thiele et al. European consensus on grading bone marrow fibrosis and assessment of cellularity. *Haematologica*. 2005;90:1128.

It is underscored that the consensus definition of aCR bone marrow is to be used only in those patients in which all other criteria are met, including resolution of leukoerythroblastosis.

It should also be noted that it was a particularly difficult task for the working group to reach a consensus regarding what represents a complete histologic remission.

‡Immature myeloid cells constitute blasts + promyelocytes + myelocytes + metamyelocytes + nucleated red blood cells. In splenectomized patients, <5% immature myeloid cells is allowed.

§See above for definitions of anemia response, spleen response, and progressive disease. Increase in severity of anemia constitutes the occurrence of new transfusion dependency or a  $\geq 20$  g/L decrease in hemoglobin level from pretreatment baseline that lasts for at least 12 weeks. Increase in severity of thrombocytopenia or neutropenia is defined as a 2-grade decline, from pretreatment baseline, in platelet count or absolute neutrophil count, according to the Common Terminology Criteria for Adverse Events (CTCAE) version 4.0. In addition, assignment to CI requires a minimum platelet count of  $\geq 25,000 \times 10^9/L$  and absolute neutrophil count of  $\geq 0.5 \times 10^9/L$ .

||Applicable only to patients with baseline hemoglobin of  $< 100$  g/L. In patients not meeting the strict criteria for transfusion dependency at the time of study enrollment (see as follows), but have received transfusions within the previous month, the pretransfusion hemoglobin level should be used as the baseline.

¶Transfusion dependency before study enrollment is defined as transfusions of at least 6 units of packed red blood cells (PRBC), in the 12 weeks prior to study enrollment, for a hemoglobin level of  $< 85$  g/L, in the absence of bleeding or treatment-induced anemia. In addition, the most recent transfusion episode must have occurred in the 28 days prior to study enrollment. Response in transfusion-dependent patients requires absence of any PRBC transfusions during any consecutive "rolling" 12-week interval during the treatment phase, capped by a hemoglobin level of  $\geq 85$  g/L.

#In splenectomized patients, palpable hepatomegaly is substituted with the same measurement strategy.

\*\*Spleen or liver responses must be confirmed by imaging studies where a  $\geq 35\%$  reduction in spleen volume, as assessed by MRI or CT, is required. Furthermore, a  $\geq 35\%$  volume reduction in the spleen or liver, by MRI or CT, constitutes a response regardless of what is reported with physical examination.

††Symptoms are evaluated by the MPN-SAF TSS. The MPN-SAF TSS is assessed by the patients themselves and this includes fatigue, concentration, early satiety, inactivity, night sweats, itching, bone pain, abdominal discomfort, weight loss, and fevers. Scoring is from 0 (absent/as good as it can be) to 10 (worst imaginable/as bad as it can be) for each item. The MPN-SAF TSS is the summation of all the individual scores (0-100 scale). Symptoms response requires  $\geq 50\%$  reduction in the MPN-SAF TSS.

‡‡Progressive disease assignment for splenomegaly requires confirmation by MRI or computed tomography showing a  $\geq 25\%$  increase in spleen volume from baseline.

Baseline values for both physical examination and imaging studies refer to pretreatment baseline and not to posttreatment measurements.

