#### 7.2.9 Assessment of response

##### Weeks 2-16

ET and PV patients will be assessed at each protocol scheduled visit for haematological response according to 2009 ELN criteria [1] (Appendix 5) by the Investigator. This will include review of the platelet count, HCT (PV only) and WBC in combination with ultrasound (if applicable) and requirement for venesection. An ultrasound is only applicable prior to 24 weeks if the patient entered the trial in haematological PR with an enlarged spleen on imaging. In these cases, an ultrasound showing a normal spleen must be obtained in order to report haematological CR when this is suspected.

For MF patients, assessment of haematological response will be performed at each protocol scheduled visit using the IWG-MRT criteria [2] (Appendix 6). "Maintenance of response" will be defined as no evidence of disease progression. Disease progression is defined in Appendix 6 but please note a bone marrow to confirm disease progression prior to 24 weeks should only be performed if clinically indicated according to local practice.

---

### Week 24

The trial bone marrow performed at week 24 will be centrally reviewed and a trephine histopathology report issued. Sites will be requested to provide an anonymised report from the latest bone marrow assessment available for each patient prior to registration to ensure a comparison report can be prepared from the trial biopsy at 24 weeks.

Central review of the bone marrow trephine sample will not be fed back in real time and therefore cannot be a guide for patient management.

Sites will then perform the 24 week response assessment upon receipt of this histopathology report using all the relevant clinical data.

For ET and PV patients, assessment of response at 24 weeks will be performed against the 2013 ELN criteria [3] (Appendix 7) using the BM report and results of blood counts (platelets, WBC, haematocrit), blood film, liver/spleen on palpation, symptom assessment (via MPN SAF) and occurrence of haemorrhagic or thrombotic events.

For MF patients, assessment of response at 24 weeks will be performed against IWG-MRT criteria [2] (Appendix 6) using the BM report and results of blood counts (haemoglobin, neutrophils, platelets), blood film for presence of immature myeloid cells and spleen on palpation.

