#### 12.1.2 Secondary outcome measures

- Proportion of patients with a reduction in the peripheral blood JAK2-V617F, CALR 5bp insertion (exon 9), or CALR 52bp deletion (exon 9) mutant allele burden of  $\geq 50\%$  at 12 weeks
- Toxicity measured as the number of grade 3 and 4 adverse events reported.
- The number of thrombotic events of any grade reported and validated.
- Haematological response, assessed at weeks 12 and 24, for patients who enter the study in response (CR or PR). Haematological response is defined according to 2009 ELN criteria for ET/PV patients and no evidence of disease progression for MF patients according to IWG-MRT response criteria (for criteria see Appendices 5 & 6).
- Proportion of patients in each response category according to IWG-MRT response criteria for MF patients and 2013 ELN response criteria for ET/PV patients at 24 weeks of treatment.
- Proportion of patients showing an improvement in response category at 24 weeks compared to baseline according to 2009 ELN criteria for ET/PV patients [1] and according to IWG-MRT response criteria [2] for MF patients. Patients who are in a higher category at week 24 compared to baseline will be classed a success. Patients who enter the trial in CR and who maintain a CR will also be classed as a success in this outcome.

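### Appendix 6 gives the minimum platelet count for clinical improvement in myelofibrosis with a number and unit that do not fit together, at 250 times the complete-response floor

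*Combined protocol and SAP*

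**What the plan says.** Section 7.2.9 (Week 24) makes Appendix 6 the tool for MF: "For MF patients, assessment of response at 24 weeks will be performed against IWG-MRT criteria". Sites make the assignment themselves once the central histopathology report arrives.

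The Appendix 6 table sets these platelet conditions (the exponent prints on the line in the quotes):

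- CR, and the first route to PR: "Platelet count ≥100 x 10 9 /L and <UNL".
- Second route to PR: "platelet count ≥50, but <100 x 10 9 /L and <UNL".
- CI: no platelet figure in the table body. The category is defined as "The achievement of anemia, spleen or symptoms response without progressive disease or increase in severity of anemia, thrombocytopenia, or neutropenia", with a footnote. That footnote adds: "In addition, assignment to CI requires a minimum platelet count of" at least 25,000 x 10^9/L, together with a neutrophil minimum of 0.5 x 10^9/L.
- Stable disease, the default: "Belonging to none of the above listed response categories".

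Section 12.1.2 uses the categories in a secondary outcome: "Proportion of patients in each response category according to IWG-MRT response criteria for MF patients" at 24 weeks. A second outcome there counts patients whose category is better at week 24 than at baseline. Section 7.1 lists improved response by the same MF criteria as one of the grounds on which continuing treatment is encouraged.

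**The concern.** The three categories run from best (CR) to least (CI), so a platelet floor for CI would be expected at or below the floors for the better categories. It is instead far above them, and far above the upper normal limit that caps CR and PR. The footnote is an operative threshold and not background, because sites are told to assign categories from this appendix.

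Two things could follow. A site that applies the footnote literally would record stable disease where the rest of the criteria give CI. A site that sees the figure cannot be meant would have to supply its own, and the protocol gives no corrected value and asks for no record of the floor used. In either case the CI count cannot be reproduced from the protocol text alone.

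**Working it through.** **Inputs.** CI platelet floor 25,000 x 10^9/L and CI neutrophil floor 0.5 x 10^9/L (Appendix 6, CI footnote). CR platelet floor 100 x 10^9/L, second-route PR floor 50 x 10^9/L, CR neutrophil floor 1 x 10^9/L (Appendix 6 table). PV/ET entry ceiling 600 x 10^9/L (Section 4.1), used for scale only because no platelet ceiling is given for MF. Recruitment minimums of 15 PV, 10 ET and 5 MF among 42 (Synopsis, Sample Size).

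**Step 1: ratios in the same unit.**

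- CI floor / CR floor = 25,000 / 100 = 250.
- CI floor / second-route PR floor = 25,000 / 50 = 500.
- CI floor / PV-ET entry ceiling = 25,000 / 600 = 41.7.

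**Step 2: is the whole sentence off scale?** CI neutrophil floor / CR neutrophil floor = 0.5 / 1 = 0.5. The neutrophil figure in the same sentence is on the expected scale, so only the platelet figure is out of line. No other section corrects it.

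**Step 3: would a unit slip explain it?** 25,000 per microlitre x 10^6 microlitres per litre = 2.5 x 10^10 per litre = 25 x 10^9/L, a factor of 25,000 / 25 = 1,000. With 25, the floors would fall in order: 100 (CR), 50 (second PR route), 25 (CI). That pattern is coherent, but it shows only that the explanation is plausible. The cited criteria were not available to confirm it.

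**Step 4: the literal consequence.** Take an MF patient with an anaemia, spleen or symptoms response, no progression and no worsening cytopenia, who misses CR and PR. With the footnote applied as printed, the patient fails CI. Progression is excluded by construction, so the default row applies: stable disease.

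**Step 5: how many patients.** The planned MF minimum is 5 of 42 = 11.9%. The arithmetic ceiling, with PV and ET at exactly their minimums, is 42 - 15 - 10 = 17. One reclassified patient moves the MF percentage by 1/5 = 20 points at the minimum and by 1/17 = 5.9 points at the ceiling. Only patients who fit Step 4 can be reclassified.

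**Step 6: what is untouched.** The primary outcome is allele burden (Section 12.1.1) and uses no platelet count. For the rule of 3 or more in 42 (Section 12.6), with X binomial(42, p): P(X >= 3 | p = 0.02) = 0.052 and P(X >= 3 | p = 0.10) = 0.805. These meet the stated one-sided 0.1 and 80%, and nothing in Appendix 6 enters them. The MF version of haematological response at weeks 12 and 24 is absence of progression, which does not use the CI footnote either.

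**The case against.** The best case against raising this is that it changes little in practice. A haematologist would see at once that the figure cannot be applied as printed. The outcomes cite the published MF criteria, so sites are pointed to a source beyond this transcription. The two outcomes concerned are reported as counts and percentages, and no decision rule depends on them. All of that stands, and it sets the severity. It does not remove the point, because the protocol's own text is what sites are told to apply and the text contradicts itself.

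A reader might infer that the misprint closes off the easiest response category for every MF patient. The documents do not support either half of that.

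- Nothing says CI is the easiest category to reach, and its routes are narrow for other reasons. A spleen response needs MRI or CT confirmation, while the schedule has only ultrasound, and a baseline spleen palpable at less than 5 cm is not eligible. A symptoms response rests on a questionnaire completed only at baseline and week 24, while benefit must last at least 12 weeks. An anaemia response needs baseline haemoglobin below 100 g/L or prior transfusion dependency.
- The footnote changes a category only for patients who clear those hurdles and miss CR and PR. The figure of 17 is a ceiling on the size of the MF group, not an expected number affected.

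A reader might also take 25 x 10^9/L as established. It is the obvious candidate, but the documents do not state it.

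**Conclusion.** The point holds as a minor error. The platelet floor for CI is incompatible with its unit: 250 times the CR floor and 500 times the lower PR floor in the same appendix. Applied literally, it sends an MF patient who otherwise meets CI, and meets neither CR nor PR, to stable disease. It reaches the MF part of two descriptive secondary outcomes (week-24 category and improvement in category) and the MF wording in the Section 7.1 continuation guidance.

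The ratios are exact. Two elements are inferences. That no MF patient could reach the printed floor is not stated, since the protocol gives no MF platelet ceiling, but it is close to certain for a value 250 times a floor that itself lies below the upper normal limit. That the cause is a per-microlitre count given a per-litre unit is plausible and unconfirmed. A reading that the trial's main conclusion is at risk has no support: the primary outcome, the decision rule and the sample size do not depend on this figure.

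**What to change.** Reconcile the number and unit in the CI footnote with the Appendix 6 table and with the cited MF criteria, and print the confirmed value. Issue that value to all sites, since sites assign the categories. If any MF patient already has a week-24 category, confirm that the confirmed floor was the one used, and correct the record where it was not. The cost is a one-figure correction, a notice to sites, and a check of a small number of MF records. No design or analysis change is needed.
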